### Randomization and blinding procedures

Following the initial assessment, eligible volunteers will be randomly assigned to two experimental groups if they meet the inclusion criteria by the secretariat of the Pulmonology Department of the GCHAA. The randomization will be carried out using sealed envelopes. Individuals will have their allocation concealed through the use of sealed envelopes that are sequentially numbered and opaque.
^
36
^ The envelopes will be opened only by the primary researcher, who is responsible for the research project and coordination of the study. The pulmonologist who will perform lung function testing on all participants (well-maintained and regularly calibrated equipment), diagnose asthma and perform the measure of chest expansion, the radiologist who will perform the ultrasonography (US), and the two separate physical therapists, who will implement the DMRT and BRE will be unaware of the group allocation.

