### Initial assessments

A pulmonologist of GOHK with years of experience diagnosing and treating asthma patients will examine the chest expansion, the pulmonary function, and diagnosis of asthma. The radiologist will perform the US assessment, and the secretariat of the GOHK will administer the questionnaires in a random order and collect all data.

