**Interventions**

The pulmonologist and the main researcher of the protocol will organize two online sessions with all the participants after the randomization. In one session, participants will be informed by the pulmonologist about (a) general asthma information, (b) asthma triggers, (c) recognition of asthma symptoms, (d) medication and proper use of asthma medications (inhaler techniques), (e) smoking, and (f) asthma control (symptom control/future risk domains/long-term goals).
^
38
^ As for the last domain (asthma control), information will be provided regarding, (i) the dynamic changes of asthma, (ii) the recognition of these changes based on PEF values and symptoms, (iii) the importance of early detection of clinical signs of worsening and the immediate initiation of appropriate medication.

At the second online session the participants will be informed by the main researcher about (a) the breathing pattern, (b) the pathological pattern of breathing that is developing both in stable phase and in paroxysm,
^
39
^ (c) the role of physiotherapy and specifically about the BRE in PR, (d) the formation of a trusting relationship between a person living with asthma and a medical professional (e) the importance of self-efficacy in asthma self-management
^
40
^
^–^
^
43
^ and (f) the self-efficacy enhancement process.

Following the two online sessions, there will be a discussion between patients and health professionals (pulmonologist - main researcher) lasting approximately one hour, during which patients can share their objectives, values, apprehensions, support and commendations. The structure of the online session will be determined by a) the long-term objectives for asthma management
^
5
^ and b) the health belief model.
^
44
^
^,^
^
45
^ Regarding the treatment sessions, every participant will receive twelve sessions twice weekly for six weeks, lasting one hour per session. Individual sessions will be provided in patients’ homes under the same conditions (
*e.g.*, day, time of day, temperature, therapeutic bed, and patient’s position).

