### Outcome measures

The evaluations will take place at three time - points: prior to treatment (week 0), post-treatment (week 6), and three months subsequent (week 12). The primary outcomes will entail the measurement of diaphragm excursion using ultrasound
^
50
^ and chest expansion (CE) using a tape measure.
^
51
^ Secondary outcomes will also be employed: maximal inspiratory and expiratory pressures (MIP/MEP),
^
52
^
^,^
^
53
^ dysfunctional breathing (Nijmegen questionnaire – - NQ),
^
54
^ asthma Control (ACT),
^
55
^
^,^
^
56
^ quality of life (SF-12v2),
^
57
^ and dyspnea (Borg scale).
^
58
^
Table 2. illustrates the SPIRIT
^
34
^ schematic protocol of the study along with the schedule of assessments.

**Table 2. T2:** Standard protocol items: recommendations for interventional trials of this study (SPIRIT).

TIME POINT	Enrollment (-T1)	Allocation (T0)	Pre-intervention (T1)	Intervention	Post-Intervention	
					(T2)	(T3)
ENROLLMENT:						
Eligibility screen	X					
Informed consent	X					
Demographic information	X					
Allocation		X				
Intervention						
MDRT + BRE						
BRE						
ASSESMENTS						
Neurological and cardiovascular assessments	X					
Primary outcomes: US			X		X	X
CE			X		X	X
Secondary outcomes: MIP/MEP			X		X	X
NQ			X		X	X
ACT			X		X	X
Borg scale			X		X	X
SF-12v2			X		X	X

-T1: one month before first treatment; T0: one week before first treatment (week 0); T1: 20 minutes before first treatment; T2: after the last treatment, (week 6); T3: follow-up 6 weeks from the last treatment (week 12).

**
*Primary outcome measures*
**

**Diaphragmatic excursion assessment with ultrasonography:** Numerous studies have confirmed the effectiveness of the US to evaluate diaphragmatic function. Since 1970,
^
59
^ the US has been utilized to assess the diaphragm’s mobility. Modern medicine accepts its use as a completely safe method. The diagnostic US has 93% sensitivity and 100% specificity.
^
17
^ The examiners are not exposed to any radiation, and there is no need for special preparation, allowing for as many safe applications as required. The US offers the option of a dynamic inspection of the affected area in real time. The diaphragmatic excursion is measured in cm/mm. In this study the excursion of the diaphragm will be measured using the ultrasound device, E-CUBE 8LE (Seoul, Republic of Korea).

**Chest wall expansion (CWE):** In clinical and research practice, the inch tape measure is an alternative method for assessing chest expansion.
^
60

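### The assessor of chest expansion, declared unaware of allocation, joins an hour-long open discussion with participants after randomisation, so blinding of that primary outcome cannot be relied on

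*Protocol article*

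**What the plan says.** All places are in the protocol article.

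- **Who measures.** Recruitment procedures, Randomization and blinding procedures, and Initial assessments all give chest expansion to the pulmonologist. Under Initial assessments, this person "will examine the chest expansion, the pulmonary function, and diagnosis of asthma".
- **Status of the outcome.** Outcome measures names two primary outcomes: diaphragm excursion by ultrasound "and chest expansion (CE) using a tape measure". Both are assessed at weeks 0, 6 and 12.
- **Declared blinding.** In Randomization and blinding procedures, one sentence lists the pulmonologist and the radiologist and ends with "the two separate physical therapists, who will implement the DMRT and BRE will be unaware of the group allocation". The statement covers everyone in the list.
- **Who knows the allocation.** Same section: "The envelopes will be opened only by the primary researcher".
- **Contact after randomisation.** Interventions: "The pulmonologist and the main researcher of the protocol will organize two online sessions with all the participants after the randomization". The pulmonologist gives one session and the main researcher the other. Afterwards "there will be a discussion between patients and health professionals (pulmonologist - main researcher) lasting approximately one hour". Its content is left to the participants and is open in scope: the article describes it as time "during which patients can share their objectives, values, apprehensions, support and commendations".
- **Reliance on blinding.** The Discussion lists blinding of examiners among the features that make the findings reliable.

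**The concern.** A blind assessor should have no unstructured contact with randomised participants outside the assessments, least of all in the company of someone who knows the allocation. Here the plan schedules such contact for the named assessor of a primary outcome. Participants are not said to be blinded, and the control arm receives the breathing exercises alone with no sham procedure. A participant who knows the arm and talks about hopes or worries can easily mention the treatment.

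Tape-measured chest expansion is the difference between readings at deep inhalation and deep exhalation. It depends on patient effort, on how the assessor encourages it, and on how the tape is read. An assessor who has learned the arm could influence all three without intending to. If so, the article's claim of examiner blinding would not hold for one of its two primary outcomes.

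**Working it through.** **1. The passages side by side**

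| Question | What the article fixes | Section |
|---|---|---|
| Who measures chest expansion? | The pulmonologist | Recruitment procedures; Randomization and blinding procedures; Initial assessments |
| Is that person declared blind? | Yes | Randomization and blinding procedures |
| Does that person meet participants after randomisation, other than to assess them? | Yes: teaches a session and joins a discussion of about one hour | Interventions |
| Who else hosts? | The main researcher; the envelopes are opened by the primary researcher who runs the project, apparently the same role | Interventions; Randomization and blinding procedures |
| Are participants blinded? | Not described; only staff are listed | Randomization and blinding procedures |
| Does the ultrasound assessor attend? | No role described | Interventions |

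The method text for chest wall expansion speaks of a therapist taking the reading. That looks like a generic description of the technique, and three other sections name the pulmonologist.

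**2. Timing**

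Table 2 puts enrolment (-T1) one month before first treatment, allocation (T0) one week before, and the week-0 measurement (T1) 20 minutes before. Two things follow.
- The interval from -T1 to T0 is about 4 − 1 = 3 weeks, enough for two sessions and a discussion before allocation.
- On Table 2's schedule the week-0 chest expansion comes after allocation. It could therefore also come after the discussion, whose exact date is not given.

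**3. Which bias would reach the planned test**

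The Statistical analysis section plans a 2×3 repeated-measures ANOVA of the group-by-time interaction. Let b₀, b₆ and b₁₂ be the difference between arms in reading bias at each visit. The interaction sees only b₆ − b₀ and b₁₂ − b₀.
- If b₀ = b₆ = b₁₂, both are zero and the bias cancels.
- If b₀ = 0 and b₆ = b₁₂ = b, the whole of b enters.

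The harm therefore comes from bias that differs between week 0 and week 6 or 12.

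**4. Illustration of size (assumed bias)**

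The documents give no SD for chest expansion and no figure for reading bias. The inputs are 12 per arm (Sample size calculation), two-sided 5% (Statistical analysis), no true effect, and an assumed differential bias d in SD units. For a two-group t-test at one time point:

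- df = 2 × 12 − 2 = 22, critical value 2.074
- noncentrality = d × √(12/2) = 2.449 × d

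| Assumed d | Noncentrality | False-positive rate, 12 per arm | Same, 10 completers per arm (df 18) |
|---|---|---|---|
| 0.2 | 0.490 | 7.6% | 7.1% |
| 0.3 | 0.735 | 10.8% | 9.7% |
| 0.5 | 1.225 | 21.6% | 18.5% |

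This is not the planned interaction test. The rate for that test would also depend on the within-patient correlation, which is not given.

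**The case against.** The strongest reply is that nothing in the text says the arm is disclosed. The sessions are common to both arms, and the physiotherapy topic is the breathing retraining that everyone receives; the manual technique is not on the list. The article does not say that participants know their arm when the discussion takes place. A full protocol might contain an instruction not to disclose it. The bias figures are assumed and would be the same for any route of unblinding. Moving the sessions would also leave the pulmonologist facing participants at weeks 6 and 12, after 12 treatment sessions.

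Much of this stands. A reader might infer any of the following, and the documents support none of them:
- That the blind is actually broken. The text shows an exposure, not a disclosure.
- That controls learn in these sessions about a treatment they will not get. The listed topics do not include it, and participants are in any case told the study methods at consent and given the protocol.
- That participants arrange their own treatment and so must know the arm by then. The article says only that sessions are provided in their homes.
- That bias at all three visits inflates the result. Bias that is constant across visits cancels from the interaction.

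What does not stand is that this is only a gap left by a condensed article. The article itself fixes the assessor, the blinding claim, the timing after randomisation and the pulmonologist's presence in an open discussion. Because the session content is the same for both arms, nothing stated requires it to follow allocation. The point about weeks 6 and 12 is correct and shapes the fix.

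**Conclusion.** The point holds as a weakness that should be fixed. The declared blinding of the chest expansion assessor is exposed by the plan's own schedule, so it cannot be relied on for that primary outcome. Diaphragm excursion by ultrasound is not touched by this route, because the radiologist has no described part in the sessions.

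The conclusion rests on two readings: that participants may know their arm at the discussion, since no participant blinding is described, and, as a lesser support, that the main researcher and the envelope-opening primary researcher are the same role. The size of any bias cannot be derived from the documents. The range of about 8% to 22% shows what assumed biases of 0.2 to 0.5 SD would do in a simple comparison of 12 per arm; it is not an estimate for this trial.

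**What to change.** 1. In Interventions, change the timing of the two online sessions and the discussion from after to before randomisation, using the roughly three weeks between -T1 and T0. Alternatively, keep the pulmonologist out of any discussion with participants after allocation.
2. In either case, add an instruction that participants do not reveal their treatment at the week 0, 6 and 12 assessments. Moving the sessions alone does not protect those visits.
3. For participants already enrolled under the current order, do not describe chest expansion as assessed blind, and qualify the statement on examiner blinding in the Discussion.

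**Cost.** For new participants this is one change of wording, one of calendar and a short instruction, with no extra staff or visits. A small downside is that some people may receive the education and then not be randomised. The trial started in January 2023 with completion scheduled for January 2024, the protocol version is dated 29/09/2023, and the article says that further modifications could not be made. Rescheduling may therefore come too late for many participants. The reporting correction in item 3 needs no design change and remains available.

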Physiotherapy intervention will be provided by two physical therapists, trained by the professor of chest physiotherapy and the professor of manual therapy respectively, at the Physiotherapy Department, UNIWA. Any departure from the administration of treatment sessions (such as missing more than one appointment) or any exacerbation of symptoms will lead to exclusion. Brief descriptions of the interventions planned for each group are provided below.

Intervention Group: This group will receive MDRT plus BRE. MDRT is intended to stretch and mobilize the diaphragmatic muscle fibers indirectly. MDRT will be applied as described by Rocha and his colleagues.
^
18
^

MDRT: Participants will be instructed to lie in a supine position with relaxed limbs. The therapist will be positioned at the patient’s head. Manual contact will be made using the hypothenar region and the last three fingers bilaterally, placed under the seventh to tenth rib costal cartilages. The therapist’s forearms will align towards the patient’s shoulders. During inhalation, the therapist will apply gentle pulling and lateral elevation of the ribs in the inspiratory phase at the points of contact. As the participant exhales, the therapist’s touch will deepen towards the inner costal margin while maintaining resistance. This connection will further deepen within the costal margin in subsequent respiratory cycles. Regarding respiratory volumes, patients will be instructed to breathe progressively deeper from set to set, aiming for maximal diaphragmatic excursion and stretch. It is essential to ensure that the therapist’s grip on the lower thoracic aperture is maintained throughout. The entire process will consist of two sets of 10 repetitions, separated by a 1-minute interval lasting 10 minutes.
^
46
^

BRE: BRE will be conducted for 30 minutes. The primary objective of these exercises is to mitigate hyperventilation, hypocapnia, and dysfunctional breathing—common symptoms in individuals with asthma.
^
47
^ The initial step involves identifying and inhibiting an abnormal upper thoracic respiratory pattern and re-education of diaphragmatic and slow nasal breathing. Additionally, brief respiratory pauses will be introduced after each exhalation.
^
48

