### Sample size calculation

The sample size calculation was based on an alpha (α) level of 0.01, a power (β) of 0.85, and a large effect size, Cohen’s d, of 1.86 for a two-tailed independent t-test. This effect size was calculated based on the results reported by Rocha et al. (2015),
^
18
^ specifically from the mean (SD) values of the control and experimental groups following six manual therapy intervention sessions. Furthermore, the calculation accounted for an anticipated attrition rate of approximately 15%, foreseeing the potential for participant dropout or exclusion. This comprehensive approach to sample size calculation ensures the robustness and reliability of the study’s findings, enabling a precise detection of the large effect size with high statistical confidence. This resulted in a total sample size of 24 people (12 per group) considering a withdrawal rate of 15%.
^
75
^

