**Data collection methods**

Data regarding the outcomes pre and post-intervention will be meticulously collected from the main researcher. The collected information will undergo a thorough examination to analyze the outcomes. Throughout the study, the professor of chest physiotherapy (supervisor) will closely oversee the main researcher administering the study’s data. To ensure the patient adheres to the study, timely messages will be sent to their mobile phones, providing information and reminders regarding upcoming sessions. A 10% drop-out rate has been considered in the sample size calculation, thus minimizing potential interference with the study results.

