**Monitoring**

**
*Data monitoring*
**

A data monitoring committee of members from the UNIWA Physiotherapy Department will periodically review the accumulating data, determining if the trial should be modified or discontinued.

**
*Harms*
**

A clinical staff is going to supervise the entire procedure. Any adverse events will be immediately reported throughout the trial to the Physiotherapy Department of the UNIWA committee.

**
*Auditing*
**

An evaluation of the experiment will be performed each month. Every deviation from the protocol will be recorded and addressed.

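### Randomised participants are excluded for missed sessions or any exacerbation, and nothing in the article keeps them in follow-up or analysis

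*Protocol article*

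**What the plan says.** The rule is in the Interventions section: "Any departure from the administration of treatment sessions (such as missing more than one appointment) or any exacerbation of symptoms will lead to exclusion". It is separate from the entry criteria, which are listed under Participants' characteristics.

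It acts after randomisation. The pulmonologist and the main researcher "will organize two online sessions with all the participants after the randomization", and only then do the treatment sessions begin: "every participant will receive twelve sessions twice weekly for six weeks, lasting one hour per session".

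The Sample size calculation section puts exclusion together with dropout: "the calculation accounted for an anticipated attrition rate of approximately 15%, foreseeing the potential for participant dropout or exclusion". Data collection methods gives a different allowance: "A 10% drop-out rate has been considered in the sample size calculation, thus minimizing potential interference with the study results".

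Statistical analysis plans a 2×3 repeated-measures ANOVA over weeks 0, 6 and 12. In its standard form this uses only participants measured at all three times. On harms, the Monitoring section says: "Any adverse events will be immediately reported throughout the trial".

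**The concern.** Randomisation makes the two groups comparable at the moment of allocation. A rule that removes people for what happens afterwards can undo that, because the reason for removal may depend on the treatment, the outcome or both.

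The exacerbation clause matters most. The Asthma Control Test asks about symptoms over the most recent four weeks, and Borg dyspnea is also an outcome. Someone whose asthma worsens during treatment would be expected to score badly on these measures, and the rule takes that person out because of the worsening. The missed-session clause is less clearly tied to outcome, but it still restricts the result to people who attend almost everything.

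With 12 per arm, one or two removals can move a group mean. Measurements that were never taken at weeks 6 and 12 cannot be recovered at the analysis stage.

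**Working it through.** **1. The plan's own sample size.** The inputs, from Sample size calculation, are "alpha (α) level of 0.01, a power (β) of 0.85, and a large effect size, Cohen’s d, of 1.86 for a two-tailed independent t-test". For n per arm, the power of the t-test uses a noncentral t with 2n − 2 degrees of freedom and noncentrality d·√(n/2).

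| Analysed per arm | Noncentrality | Power at 0.01 | Power at 0.05 |
|---|---|---|---|
| 8 | 3.72 | 0.757 | 0.933 |
| 9 | 3.95 | 0.830 | 0.959 |
| 10 | 4.16 | 0.883 | 0.975 |
| 12 | 4.56 | 0.948 | 0.992 |

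Ten per arm is the smallest number that reaches 0.85 at alpha 0.01. Then 10 / 0.85 = 11.8, so 12 per arm and 24 in total, which reproduces the stated figure. A 10% allowance gives 10 / 0.90 = 11.1, also 12 per arm, so the 15% versus 10% discrepancy does not change N. The plan therefore has room for two losses per arm, and exclusions count among them.

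**2. How many the missed-session clause could remove.** The article gives no attendance rates. Assume each of the 12 sessions is missed independently with probability p. The chance of missing more than one is 1 − (1 − p)^12 − 12p(1 − p)^11.

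- p = 0.02: 1 − 0.785 − 0.192 = 2.3%
- p = 0.05: 1 − 0.540 − 0.341 = 11.8%
- p = 0.10: 1 − 0.282 − 0.377 = 34.1%, or about 8 of 24, leaving about 16 (8 per arm)

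Exacerbations would add to these figures.

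**3. What one-sided losses could do.** Assumptions: no true effect, outcome SD 1, and two of 12 removed from one arm only. The two removed are those with the lowest value of a score that correlates with the outcome at r. The two lowest of 12 standard normal values have expected values −1.629 and −1.116, so the remaining ten have an expected mean shift of r × (1.629 + 1.116) / 10 = 0.2745r. Type I error of a two-sided t-test at 0.05 (10 versus 12) comes from 400,000 simulated trials.

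| r | Shift (SD) | Type I error |
|---|---|---|
| 0.3 | 0.08 | 5.5% |
| 0.5 | 0.14 | 6.4% |
| 1.0 | 0.27 | 11.3% |

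Runs of 40,000 trials vary from these by about 0.01 SD and 0.1 percentage points. If two are removed from each arm with the same r, the expected shifts cancel and the between-arm bias is zero.

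**4. Whether exclusion is needed to protect power.** Keeping all 24 gives 0.948 at alpha 0.01 if the effect is undiluted. If 15% of the effect is lost because the retained participants gain nothing (assumed), d = 1.86 × 0.85 = 1.58 and power is 0.841, close to the planned value. At 25% dilution, d = 1.40 and power is 0.72 at alpha 0.01 and 0.90 at 0.05.

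**The case against.** The strongest reply concerns scope. The sentence stands among the descriptions of treatment delivery and does not say whether exclusion is from treatment, follow-up or analysis. An analysis plan that is not shown could define an all-randomised set. This stands as a limit on certainty. Against it, the sample size is inflated for exclusion, "foreseeing the potential for participant dropout or exclusion", which would be unnecessary if those people were still measured and analysed. Nothing in the article says that they are.

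A reader might go further and infer three things that the documents do not support.

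- *That any benefit is biased upward.* The rule applies to both arms. If exacerbations were more common with breathing retraining alone, the control arm would lose its worst cases and the bias would run against the manual technique.
- *That the manual-therapy arm is more exposed because it has two components to depart from.* The only example of departure is missed appointments, and both arms have the same twelve sessions.
- *That the type I error is 11% or the power 0.76.* The first needs one-arm losses and a correlation of 1.0. The second needs 8 per arm and alpha 0.01. At the 0.05 level named under Statistical analysis, power with 8 per arm is 0.93.

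The link with outcome is also weaker for the primary measures, ultrasound excursion and tape-measured chest expansion, than for symptom scores. The reminder messages in Data collection methods may keep missed sessions rare. Adverse events are to be reported throughout, so exacerbations need not vanish from the safety record. That reporting does not return the participant to the efficacy comparison. Finally, the trial is labelled an equivalence study, for which an adherent-set result is informative. That argues for reporting both sets, not for removing participants.

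**Conclusion.** The point holds as a threat to validity. It is not an error in the sample size, which reproduces. The article states a rule that excludes randomised participants for post-randomisation events, budgets for them as lost, and nowhere retains them. Read as loss from analysis, which is the better-supported reading but not an explicit one, the trial would compare adherent, exacerbation-free subsets, even with balanced exclusions.

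Bias between arms is a possibility of unknown sign. It requires exclusions that differ by arm or relate differently to outcome. With two of 12 lost from one arm, the illustrative range runs from slight (0.08 SD, 5.5%) to material (0.27 SD, 11.3%), depending on an assumed correlation. Loss of more than two per arm would take power below 0.85 at alpha 0.01, but not at 0.05 with 8 or more per arm. All attendance rates and correlations are assumptions. The rule should be changed because it can lose data for good and is not needed to reach the planned power under modest dilution.

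**What to change.** Replace the exclusion clause with wording such as: participants who miss sessions or have an exacerbation remain in the trial, are assessed at weeks 6 and 12, and are analysed in the group to which they were randomised. Keep the adherent set only as a labelled sensitivity analysis, and report exacerbations by arm. Whether treatment sessions continue after an exacerbation is a clinical decision and is not addressed here.

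The cost is a change of wording, a few more attendances at visits that are already scheduled, and a possibly smaller estimated effect because non-adherent participants are included. The change would be notified to the Ethics Committee. The article says both that modifications will be disclosed to that committee and that no further modifications could be made, so those two statements need reconciling. Since the study started in January 2023, anyone already excluded should be counted by arm and reason and, where the week 6 or week 12 visit is still ahead, invited to it.
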